#### Secondary aims

Analyses for three secondary aims are also planned. The first of these analyses tests the primary hypothesis using the secondary outcome variable (cumulative combined D_12_FS increment). As a part of this analysis we will evaluate whether the D_12_FS increment result provides a conclusion for the trial in shorter time. Second, we will compare the intervention's preventive effects on root surfaces as distinct from coronal surfaces. Third, we will examine the impact of lozenge consumption itself on caries prevention in the control subjects, to check whether increased salivary flow might account for differences in the development of new caries, again using the primary and secondary outcomes.

## Discussion

The results of X-ACT should bring some clarity to the controversy over the effectiveness of xylitol as a caries preventive agent. Criticism of available evidence has focused on the design of many of the studies, as well as the heterogeneity of the results [5-7,18]. The lack of placebo controls in many of the trials increases the risk of bias and makes it difficult to disentangle the therapeutic effects of xylitol from the preventive effects of stimulating saliva flow and scrubbing tooth surfaces with gum. In addition, many of the available studies have been evaluated as being at high risk for bias for a variety of other problems, including lack of examiner blinding, lack of examiner calibration, extensive examiner variation, differences at baseline due possibly to classroom or school-level randomization, and high attrition [5,18]. X-ACT employs an active placebo control, is randomized, is adequately powered to detect any caries preventive effect of clinical significance, and adheres to strict standards for good clinical practice. Thus, the results it provides should substantially augment the existing evidence concerning the effectiveness of xylitol.

Further, and perhaps just as importantly, the results will extend this knowledge of effectiveness to adults, for whom so little effectiveness information concerning any caries preventive intervention is currently available. If xylitol lozenges prove to be effective in reducing caries increments in caries-active adults, the intervention would offer such individuals who either do not utilize dental services regularly, or who do not receive caries preventive treatment in the dental office a relatively low-cost, user-controlled caries preventive method.

The inclusion of non-cavitated lesions in the secondary analysis raises some interesting issues with regard to the relative weight given these lesions in the analysis compared to cavitated lesions. We have stated *a priori *our weighting scheme, but plan to analyze variations on this matrix to determine the sensitivity of the increment scores to several of our weighting decisions. Also, because both cavitated and non-cavitated lesions are recorded in this trial, the results should offer insight into the possibility of shortening caries trials by basing the principal analysis on non-cavitated lesion increments. Should a shorter trial be shown to be feasible in retrospect, this will have important implications for future caries trials. The typical three year duration and associated costs of such trials, has contributed to the reduction in such controlled studies in recent decades. Yet the need for this type of unbiased research result for caries preventive agents is undiminished, as discussed above.

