### Study Schedule

Figure 1 summarizes the trial flow from a participant's perspective. The study requires a participant to visit the clinic a minimum of 5 times. Screening was followed as soon as possible by an enrollment visit. The enrollment visit is followed by a placebo run-in period. Adherent, eligible enrollees were randomized at the baseline visit. Participants are then scheduled to return at 12 months, 24 months and 36 months for caries examinations, with quarterly telephone contacts between examination visits. Before the 24-month visits began, the final examination schedule was shifted to 33 months, to adjust for slower than expected completion of enrollment.

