### Randomization and Treatment Contacts

Those enrollees who completed the run-in period with adequate self-reported adherence (consumption of more than half of lozenges scheduled during the run-in period) and who indicated a willingness to participate in the full trial attended a baseline visit wherein eligibility criteria were confirmed, and a caries examination was performed. Eligible enrollees were randomized to either the active or placebo arm, additional information was collected, and the initial supply of lozenges was dispensed. Randomization was carried out using a web-based randomization application process. Allocation assignments were stratified by site and age group (≥ 50, < 50 yrs.) in permuted blocks of varying sizes within each stratum. Staff and participants were blinded to treatment assignment. A total of 691 participants were randomized, 92% of the goal of 750.

In the periods between the visits for caries examinations, participants are contacted by telephone on a quarterly basis to assess adherence, side effects, receipt of preventive dental care; to screen for possible serious adverse events; and to arrange for re-supply of lozenges. Participants are asked how many unopened bottles they have on hand, and sufficient bottles for the next three months are dispensed from the participant's master supply at the clinical site and are delivered by courier.

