### Sample Size

We based our required sample size on a series of large longitudinal cohort studies that permitted estimates of expected combined net D_2_FS increment in the placebo group of the trial. These studies, reviewed by Griffin et al. [16] and Thomson [1] did not include measurement of D_1 _lesions. Although they varied in design, these studies reported sufficient data to calculate reasonable values for three-year untreated incidence rates of root, coronal, and total caries, under the assumption of constant rates over years. These estimated surface increments were 1.4, 2.5 and 3.7 respectively. We estimated the sample size needed, using a range of values (2.3 to 4.9) for the placebo cumulative, combined D_2_FS increment over three years, and assuming that the treatment might result in a 20% reduction, with power set at 80% and one-sided alpha at 0.025. Using PASS 2005 with a Poisson regression model and a large, but plausible overdispersion parameter (3.0, to account for excess variability), and assuming attrition of 10% per year, we obtained a sample size target of 250 at each clinical site (750 total).

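### The Discussion claims adequate power for any clinically significant effect, but the trial was sized for a 20% reduction at about the central placebo rate, and power was not restated at 691 participants and 33 months

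*Protocol article*

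**What the plan says.** The protocol article's Sample Size section derives three-year placebo increments for root, coronal and total caries from cohort studies: "These estimated surface increments were 1.4, 2.5 and 3.7 respectively". It then sizes the trial "using a range of values (2.3 to 4.9) for the placebo cumulative" combined increment, "assuming that the treatment might result in a 20% reduction, with power set at 80% and one-sided alpha at 0.025". The other inputs are a Poisson regression model in PASS 2005, overdispersion 3.0 (described as large but plausible) and attrition of 10% per year. The result is 750 participants.

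Two later changes are reported openly. Under Randomization and Treatment Contacts: "A total of 691 participants were randomized, 92% of the goal of 750". Under Study Schedule: "the final examination schedule was shifted to 33 months, to adjust for slower than expected completion of enrollment". No section restates power after either change.

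The Discussion nevertheless says that the trial "is adequately powered to detect any caries preventive effect of clinical significance". No section says what size of effect counts as clinically significant. The 20% reduction is a planning value and is not presented as the smallest effect that matters.

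**The concern.** The claim covers every effect that matters clinically, whereas the calculation behind it covers one effect size. That calculation yields 750 at only part of the placebo range it lists, and it describes a larger and longer trial than the one now under way. Participants times months fell to (691 × 33)/(750 × 36) = 84% of plan.

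The Discussion uses the claim to support the trial's weight as evidence on a disputed question. If it stands, a non-significant result could be read as ruling out any worthwhile benefit, although power for the planning effect itself depends strongly on a placebo rate not known in advance.

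**Working it through.** **Inputs.** From Sample Size: one-sided alpha 0.025 (z = 1.96), power 80% (z = 0.8416), rate ratio RR = 0.80, overdispersion φ = 3.0, three-year placebo mean μ = 2.3, 3.7 or 4.9, constant rates, attrition 10% per year. From the later sections: 691 randomized, 33 months. Assumed: 1:1 allocation, and the standard Poisson-regression formula for a binary covariate as the PASS method.

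**Reproducing 750.**

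N = φ[1.96·√4 + 0.8416·√(2 + 2/RR)]² / (μ·(ln RR)²)

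= 3 × (3.920 + 1.785)² / (μ × 0.0498) ≈ 1,961/μ completers.

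- μ = 3.7: 530 completers. Dividing by 0.9³ = 0.729 gives 727; dividing by 0.70 (a flat 30% loss) gives 757. These bracket 750.
- μ = 2.3: 853 completers, 1,170 randomized (at 0.729).
- μ = 4.9: 400 completers, 549 randomized (at 0.729).

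The target therefore corresponds to a mean of about 3.7, which the article does not say outright.

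**Power now, on the sizing convention.** Completers are 691 × 0.729 = 504, and the mean becomes μ × 33/36.

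Power = Φ{[√(Nμ/φ)·|ln RR| − 1.96·√4] / √4.5}

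At 3.7 the scaled mean is 3.39, √(504 × 3.39/3) = 23.86, and (23.86 × 0.2231 − 3.920)/2.121 = 0.66, so power is 74.6%.

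| Three-year placebo mean | 2.3 | 3.7 | 4.9 |
|---|---|---|---|
| 750, 36 months, dropouts discarded | 62% | 81% | 90% |
| 691, 33 months, dropouts discarded | 55% | 75% | 85% |
| Same, Wald formula | 51% | 71% | 82% |
| Same, first formula, attrition matched to 33 months (0.9^2.75 = 0.748) | 56% | 76% | 86% |
| Detectable reduction at 80% power (first formula, 0.729 retained) | 26% | 21% | 19% |

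**Crediting partial follow-up.** The planned model has a log person-years offset. With 10% annual loss, mean exposure to 33 months is (1 − 0.9^2.75)/(−ln 0.9) = 2.39 years, or 0.796 of three years. Using all 691 with mean 0.796μ:

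- μ = 3.7: 81% (first formula), 78% (Wald).
- μ = 2.3: 62% and 58%.
- μ = 4.9: 90% and 88%.

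**Negative binomial variance.** The planned analysis is negative binomial, so the variance-to-mean ratio is 1 + kμ rather than constant. Assume that k is set so that this ratio is 3.0 at μ = 3.7: k = 2/3.7 = 0.54. The variance of the log rate ratio is then (2/N)(1/m₀ + 1/m₁ + 2k), where m₀ and m₁ are the arm means. With person-time credited approximately, by giving everyone the mean exposure:

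- μ = 3.7: m₀ = 2.945, m₁ = 2.356, SE = 0.0731, power 86%.
- μ = 2.3: m₀ = 1.830, m₁ = 1.464, SE = 0.0818, power 78%.

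With dropouts discarded the same model gives about 68% at 2.3, 76–77% at 3.7 and 80% at 4.9.

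**The case against.** The strongest reply is that the 75% and 55% figures come from the least generous accounting. Discarding every dropout is a sizing convention. The planned analysis is intent-to-treat on all randomized participants, uses a person-time offset and imputes for those with no annual visit. On that footing, power at 3.7 straddles or exceeds 80%. The 55% also holds overdispersion at 3.0 at every mean, which the negative binomial model does not do. The article itself calls 3.0 large, eligibility selects people with a current or recent cavitated lesion, and covariates such as baseline caries severity may add precision. At the central rate the detectable reduction moves only from 20% to about 21%. Both changes to the trial are disclosed, and no endpoint or decision rule depends on the Discussion sentence.

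Most of this stands. A reader might infer that the trial is underpowered at its central rate, or that it would miss a true 20% reduction one time in four. The documents do not support that as a flat statement: it is true on one convention and not on the one closest to the planned analysis. Nor do they support reading low power for reductions below 20% as failure on a clinically significant effect, because no threshold is defined.

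Two things survive. With no threshold defined, the word *any* has no support. And at 2.3, inside the plan's own range, every variant above falls short of 80%. Even with no dropout at all, fixed overdispersion gives only 68%. The negative binomial variant would reach about 81% there, but only by setting aside the attrition the plan assumes. The possible gains from covariates or from lower overdispersion cannot be quantified from the article.

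**Conclusion.** The Discussion sentence is wrong as written, and power should have been restated once enrolment and follow-up changed. The original target of 750 is not in error: it reproduces at a placebo mean of about 3.7.

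At 691 participants and 33 months, power for a 20% reduction is about 75% at 3.7 on the sizing convention, 78–81% with dropouts' person-time credited, and about 86% if the variance is also negative binomial as calibrated above. The central shortfall is modest and may be nil. At 2.3 the corresponding figures are 55%, 58–62% and 78%, so the low end of the planning range is not adequately powered. At 4.9 power is at or above 80% on all of these accountings.

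These results rest on 1:1 allocation, constant rates, the stated attrition and the assumed PASS formula. The 75% and 55% should not be quoted without their convention.

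**What to change.** In Sample Size, add power for a 20% reduction and the detectable reduction at 691 randomized and a 33-month final examination, across placebo means of 2.3 to 4.9. Name the attrition convention (dropouts discarded, or person-time credited) and the variance model (fixed overdispersion of 3.0, or negative binomial with its dispersion value).

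In the Discussion, replace the claim about any clinically significant effect with the specific reduction and placebo rate for which about 80% power holds. With overdispersion fixed at 3.0, a 20% reduction has 80% power at a three-year placebo mean of about 1,961/(504 × 33/36) = 4.2 if dropouts are discarded, or about 1,961/(691 × 0.796) = 3.6 if their person-time is credited.

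The cost is wording and a less favourable stated claim. No enrolment, follow-up or analysis changes.
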